#### Sample Size Calculation

Based on the largest survey study conducted in France by Vuagnat and colleagues (2019) (4), we estimated that 12.4% of the population will be readmitted for suicidal attempt within the 3 months following a first suicide attempt that led to hospitalization. This is also in accordance with the study from Spirito and colleagues (2003) (6) conducted in a comparable sample of youth individuals (12%). Using the Wald Confidence Interval method, we calculated that a sample of 200 participants will be sufficient to reach a precision of +/– 4% calculated as 95 CI = p +/– 1.96 sqrt (p (1–p)/n), with *p* = 0.124.

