### Statistical Analysis

Statistical analysis will be performed using R software version 4.02. The significance level alpha will be set at 0.05, and all statistical tests will be 2-tailed.

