When interpreting our results, we will take into account potential limiting factors. First, since all inclusions will take place in Edouard Herriot University Hospital, we expect a center-effect bias. Inpatients of our unit may have more severe disorders and suicidal behaviors. Besides, patients admitted to the unit do not exhibit severe behavioral problems nor are hospitalized without consent, which may exclude a certain group of suicide attempters. This could lead to a lack of representativity and limit the external generalizability of the results. Second, loss to follow-up is common in longitudinal studies and could potentially cause selection bias. In our study, we have not included the risk of drop-outs in the calculation of the number of subjects needed. However, a follow-up period extending over a relatively short period of 3 months could reduce loss to follow-ups. To further limit this bias, we prefer phone calls at 3 months over face-to-face consultations. If the patient could not be reached, we set up a 3-level data retrieval process by gathering information from his/her designated trusted person, contacting his/her primary care physician, and finally by consulting his/her medical records. In further cases of inability to obtain information, we have planned a statistical management of missing data. Third, COVID-19 pandemic occurred during the inclusion phase. Recruitment was slowed down due to fluctuating demand for access to care, and to the reorganization of the Department of Psychiatry in our University Hospital. Psychosocial distress due to the pandemic and its consequences could modify suicidal behaviors (71). In addition, there may be stress and inflammation confounding bias related to the COVID-19 status of some inpatients. From March 2020, every patient underwent a SARS-CoV-2 RT-PCR upon admission and only those who were negative were hospitalized in the unit, thus, there was no COVID-19 positive inclusion in this study. Nonetheless, we cannot rule out the possibility of such patients being included prior to the systematic implementation of COVID-19 testing, when the virus circulation was lower in France, i.e., from approximately November 2019 to February 2020. *Post-hoc* subgroup analyses could be needed to assess the impact of potential COVID-19 infection during this time period. Either way, it would be interesting to compare the repercussions of the COVID-19 pandemic on the onset of suicidal behaviors in a future study.

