## Trial Status

The recruitment of patients into the trial began in May 2018 and is scheduled to end in October 2022. Preliminary analyses conducted on a sample of the 73 first patients of the cohort (70.8% females; mean age: 19.72 years, SD 2.44) revealed a re-attempt rate at 3 months of 17.81%, supporting a trend toward a higher risk of suicide re-attempt in this population as compared with the literature on adults.

V7 (12/07/2021): MS5 Addition of several blood tests; update of associated investigators and other study stakeholders, update of scientific collaborators.

V6 (04/22/2021): MS4 18 months extension of the recruitment period of the study, as a consequence of COVID-19.

V5 (03/30/2020): MS3 12 months extension of the recruitment period of the study.

V4 (06/03/2019): MS2 12 months extension of the recruitment period of the study.

V3 (07/26/2018): MS1 modification of the inclusion criteria, extension of the study to minors from 16 years of age, and 6 months extension of the recruitment period of the study.

V2 (02/08/2018): Approval of the initial protocol by the ethics committee.

V1 Initial protocol before submission to the ethics committee.

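### The sample-size formula gives a precision of ±4.6 percentage points with 200 participants, not the stated ±4; ±4 would need 261

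*Protocol article*

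**What the plan says.** Under Sample Size Calculation, the protocol article takes its planning rate from a French survey: "we estimated that 12.4% of the population will be readmitted for suicidal attempt within the 3 months" after a first attempt that led to hospitalisation. It adds that a second study, in young people, found about the same rate (12%).

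The method is given as "Using the Wald Confidence Interval method". The formula is printed with its multiplier of 1.96 and with p = 0.124: "calculated as 95 CI = p +/– 1.96 sqrt (p (1–p)/n" (closing bracket follows). The result is that "a sample of 200 participants will be sufficient to reach a precision of +/– 4" per cent. Since p is a proportion and the formula gives an absolute half-width, this means ±4 percentage points.

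Two other places bear on the figure without being part of the calculation. The limitations paragraph of the Discussion says "we have not included the risk of drop-outs in the calculation of the number of subjects needed". Trial Status reports that an analysis of the first 73 patients "revealed a re-attempt rate at 3 months of 17.81" per cent.

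**The concern.** The sentence gives a formula, every input and a result, so it can be checked in one line, and the result does not follow. This is not a detail that a journal article leaves to a fuller document, because no separate analysis plan could make the sentence true as it stands.

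The primary objective is to estimate the 3-month re-attempt rate, and this precision is the only reason given for enrolling 200 people. The section on the primary outcome then compares the observed rate with 12.4%, and the Introduction expects a higher early risk than in adults. The width of the interval therefore governs what the study can say about its main question. A reader who relies on ±4 points will expect a sharper estimate than the design gives.

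**Working it through.** **Inputs**, all from the Statistical Analysis section of the protocol article:
- p = 0.124, n = 200, 95% Wald interval, multiplier 1.96 (Sample Size Calculation)
- two-sided alpha: "The significance level alpha will be set at 0.05, and all statistical tests will be 2-tailed" (opening paragraph)

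**Attempt to reproduce the stated figure**

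Half-width = 1.96 × sqrt(p(1 − p)/n)

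- p(1 − p) = 0.124 × 0.876 = 0.108624
- 0.108624 / 200 = 0.00054312, with square root 0.023305
- 1.96 × 0.023305 = **0.0457**, or ±4.6 points
- Interval: 0.124 ± 0.0457, or about 7.8% to 17.0%

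The stated ±4 is not reproduced. The ratio 0.0457 / 0.04 = 1.14, so the interval is about 14% wider than stated.

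**Sample size that ±4 points would need**

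n = 1.96² × p(1 − p) / 0.04² = 3.8416 × 0.108624 / 0.0016 = 260.8, so **261**. The planned 200 is 61 short, and 61 / 261 = 23%.

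**Could another reading give ±4 with 200?**

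| Reading | Half-width at n = 200 | n for ±4 points |
|---|---|---|
| As printed (p = 0.124, 1.96) | 4.57 | 261 |
| p = 0.12, the second cited rate | 4.50 | 254 |
| Wald with continuity correction | 4.82 | not computed |
| Wilson interval | 4.58 | not computed |
| Multiplier 1.645 | 3.83 | 184 |

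None yields ±4 together with n = 200. The multiplier 1.645 also contradicts the printed 1.96 and the two-sided 5% level. Rounding does not help, since 4.57 rounds to 5 and only truncation gives 4. With 1.96 and n = 200, ±4 points would require a rate of about 9.2%. A half-width of 4.5 points at p = 0.12 needs n = 200.3, so a misprinted 4.5 is a possible origin. That is conjecture, and the text says 4 and p = 0.124.

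**Context: the same formula under other conditions**

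| Rate | Outcomes obtained | Half-width (points) |
|---|---|---|
| 12.4% | 200 | 4.6 |
| 12.4% | 180 (10% missing, assumed) | 4.8 |
| 12.4% | 160 (20% missing, assumed) | 5.1 |
| 17.81% | 200 | 5.3 |
| 17.81% | 180 (10% missing, assumed) | 5.6 |
| 17.81% | 160 (20% missing, assumed) | 5.9 |

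The article gives no loss rate, so 10% and 20% serve only to show a range.

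**The case against.** The arithmetic cannot be answered, but its weight can be disputed. The gap at the planning rate is 0.57 of a percentage point. No stopping rule, success threshold or decision rule in the article depends on ±4. The design, the estimand and the number of patients can all stay as they are. This is fair, and it limits the point to a misstated figure. It does not remove the point, because that figure is the only justification for the sample size.

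A reader might infer more than the document supports:

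- **That the study is too small and must recruit 261.** The article does not say why ±4 points would be needed, so missing it by 0.6 of a point does not show that 200 is inadequate.
- **That the missing drop-out allowance is a second error.** The Discussion discloses it as a limitation, describes retrieval through a trusted person, the primary care physician and medical records, and mentions planned handling of missing data. It means only that 4.6 points assumes all 200 outcomes are known.
- **That the preliminary 17.81% shows the planning rate to be wrong.** It comes from 73 patients, is itself imprecise and was observed after planning. It shows how the width would change and is not an error in Trial Status.
- **That the Wald method is the fault.** The article names Wald for planning and fixes no interval method for the final report. The Wilson half-width is practically the same (4.58), so the choice of method neither causes nor cures the discrepancy.

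**Conclusion.** The stated precision is wrong as written. Under the article's own formula and inputs, 200 participants give a 95% half-width of 4.6 percentage points at 12.4%, and ±4 points would need 261 evaluable participants. This conclusion uses only printed inputs and needs no outside source or assumption.

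The figure must be corrected because it carries the whole sample-size justification for the primary objective. Its consequence is moderate: a somewhat wider interval than promised, with no bias and no effect on the validity of the study. The widths under missing outcomes rest on an assumed loss of 10% to 20%, and those at 17.81% on a preliminary rate. Both sets are context only.

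**What to change.** Keep n = 200 and replace the precision statement under Sample Size Calculation with, for example:

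> With 200 evaluable participants and an expected rate of 12.4%, the 95% CI half-width is 4.6 percentage points.

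Optionally add a sentence of context, with each figure tied to its own rate: at 12.4%, the half-width would be 4.8 or 5.1 points if 10% or 20% of outcomes were missing (assumed range); at the preliminary rate of 17.81%, it would be 5.3 points with all 200 outcomes. A missing-outcome figure should not be given without its rate, because the same losses at 17.81% give 5.6 to 5.9 points.

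The cost is one sentence and a slightly less favourable stated figure. No extra patients are needed, and neither the design nor the analysis changes.

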#### Primary Outcome

First, the classic incidence rate will be calculated by dividing the total number of new re-attempt cases by the total number of suicide attempters. Next, the person-time incidence rate will be calculated by dividing the total number of new re-attempt cases by the sum of the person-time of attempters. This proportion will be compared to the estimated 12.4% based on the literature.

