Altogether and despite the known burden of youth suicide, this population has been poorly investigated and there is scarce knowledge regarding the potential factors that may differentiate those who will make repeated attempts from those who will not. Therefore, this study is aimed to define the incidence of suicide re-attempt in young first-attempters, and to investigate the association between socio-demographic, clinical, and biological (HPA axis activity with blood and hair cortisol, pro-inflammatory markers with CRP, fibrinogen, orosomucoid and IL-6, infection with *toxoplasma gondii*, and neuroplasticity imbalance measured by the proportion of mature, and pro-BDNF isoforms) variables. Given their specific characteristics, we hypothesize that young first-attempters would be at higher risk of early suicide re-attempt compared to adults.

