### Study Design

The overall study design is shown in Figure 1. According to our sample size calculation (see below), 200 adolescents and young adults will be recruited in the study. Upon enrollment, baseline data will be collected. Clinical and socio-demographic data will be investigated through the computerized clinical chart and through relatives if necessary. Psychiatric diagnoses will be established according to the Diagnostic and Statistical Manual of Mental Disorders, Fifth edition (DSM-5) during a standardized psychiatric interview. During hospitalization, participants will complete standardized and validated questionnaires. The morning after admission to the emergency unit, a first blood sample will be taken from fasting patients at 7:00 am for biological measurements. Two other blood samples will be collected and stored at −80°C for future research purposes (one EDTA sample and one PAXgene blood RNA tube). Patients who are not fasting will be rescheduled. All inpatients will benefit from usual psychiatric care and will receive appropriate referrals upon discharge. They will also be integrated into the VigilanS brief contact intervention program (23), which is currently being rolled out nationally, and has demonstrated efficacy in reducing suicide re-attempts (24).

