### Outcomes

Three months after the initial hospitalization for a first suicide attempt, participants will be contacted by phone to retrieve the primary outcome: the presence or absence of a second suicide attempt *(re-attempt)* within the first 3 months following the first suicide attempt. The data will be collected by a nurse blinded to the patients' initial characteristics, and will be further controlled by 3 independent reviewers to avoid misclassification. Other information regarding recent life events and received care will be gathered. If the patient cannot be reached, their trusted person, previously designated by the patient, will be contacted. In case of no reply, the primary care physician or medical records will be consulted. A suicide attempt is defined as a non-fatal self-directed potentially injurious behavior with the intent to die as a result of the behavior. Secondary outcomes will be baseline socio-demographic, clinical, and biological factors.

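### The 12.4% benchmark counts hospital readmissions and is not shown to be an adult rate, so a difference from it cannot be read as youth being at higher risk than adults

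*Protocol article*

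**What the plan says.** **The benchmark.** Protocol article, Sample Size Calculation: "we estimated that 12.4% of the population will be readmitted for suicidal attempt within the 3 months", the index event being a first attempt that itself led to hospitalization. The rate is given for the population, with no age group attached. The same paragraph supports it with a 12% figure from a youth sample described as comparable.

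**The study outcome.** Protocol article, Outcomes: "the presence or absence of a second suicide attempt" within 3 months. An attempt is a non-fatal, potentially injurious, self-directed act with intent to die, and admission is not part of the definition. On ascertainment, "participants will be contacted by phone to retrieve the primary outcome". If the patient cannot be reached, the trusted person is contacted, and after that the primary care physician or the medical records. Three independent reviewers check the classification. The call also gathers information on care received.

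**The comparison.** Protocol article, Primary Outcome: "This proportion will be compared to the estimated 12.4% based on the literature".

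**The question it serves.** Protocol article, Introduction: "we hypothesize that young first-attempters would be at higher risk of early suicide re-attempt compared to adults". Trial Status already reads 17.81% in the first 73 patients as a trend in that direction against the adult literature.

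**The setting.** Study Design places all participants in a national brief-contact programme that the article credits with reducing re-attempts.

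**The concern.** A comparison with a fixed literature rate shows an age effect only if the reference counts the same event, comes from the other age group, and was observed under similar care. The article establishes none of the three:

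- The reference counts readmissions. The study counts re-attempts whether or not they led to admission.
- The reference is not described as adult, and the figure offered in its support is a youth figure.
- The cohort receives a programme said to lower the event rate. The article does not say whether the reference population received it.

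The age conclusion is at stake. An excess over 12.4% could come from the wider endpoint, and a result near 12.4% could reflect the programme. The limitations in the Discussion cover centre effect, loss to follow-up and COVID-19, but mention neither the endpoint difference nor the programme.

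**Working it through.** **1. The plan's own figure.** Inputs from Sample Size Calculation: p = 0.124, n = 200, stated precision 4 points either way. Its formula gives 1.96 × sqrt(0.124 × 0.876 / 200) = 0.0457, or 4.57 points (7.8% to 17.0%). The stated 4 points would need 1.96² × 0.124 × 0.876 / 0.04² = 260.8, so 261 participants. The stated precision does not reproduce. That is a separate matter and nothing below depends on it. It does confirm that the study was sized for the precision of an estimate, not for power against 12.4%.

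**2. The definitions side by side.**

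| | 12.4% reference | Study figure |
|---|---|---|
| Event | Readmission for a suicide attempt | Any non-fatal re-attempt with intent to die |
| Admission required | Yes | No |
| Source | Cited French study | Phone, then trusted person, then physician or records |
| Age group | Not stated | 16 to 25 years |
| Contact programme | Not stated | All participants |

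I take the compared figure to be the simple proportion. The sentence follows directly on a person-time rate, which is on a different scale from 12.4%.

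**3. Illustration of the endpoint difference alone.** Let f be the share of re-attempts that lead to readmission. The documents do not give f, so it is assumed here. Assume also that both sources apply the same definition of an attempt and that no other bias acts. If the cohort's readmission risk is exactly 12.4%, its expected re-attempt proportion is 0.124 / f.

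The Primary Outcome section names no test. If an exact two-sided binomial test at the article's general 5% level were used with n = 200 and a null value of 0.124, it would declare the rate high at 35 or more events (35/200 = 17.5%).

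| f (assumed) | Expected proportion | Probability of 35 or more events |
|---|---|---|
| 1.0 | 12.4% | 2.2% |
| 0.9 | 0.124/0.9 = 13.8% | 8% |
| 0.8 | 0.124/0.8 = 15.5% | 24% |
| 0.7 | 0.124/0.7 = 17.7% | 56% |

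**4. The preliminary figure.** From Trial Status, 17.81% of 73 is 13 events. The exact 95% CI for 13/73 is 9.8% to 28.5%, and the exact two-sided p-value against 12.4% is 0.16. These data do not establish an excess.

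**5. Whether any 3-month adult figure is given.** The article states two reference rates at 3 months: 12% in youth (Introduction and Sample Size Calculation) and 12.4% with no age group. No 3-month rate is labelled adult.

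**The case against.** The strongest reply is that the primary objective is to determine a rate. The sample size rests on precision, no test is attached to the comparison, and a condensed article may leave the details to a fuller document. This stands as far as the estimate goes: incidence with its confidence interval is sound whatever the benchmark means. It does not rescue the comparison, because the article itself states both definitions, the comparison, and the youth-versus-adult reading.

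A second reply is that the gap between the endpoints may be small. The Introduction describes the 12% youth figure as re-attempts, and it lies close to the 12.4% readmission figure. This has weight and is why the table in the working is an illustration and not an estimate. The two populations may differ, however, so the agreement does not show that f is near 1. A youth figure also cannot serve as the adult reference.

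A third reply is that other influences may lower the study rate: the contact programme, under-reporting by phone, loss to follow-up, and the restriction to non-fatal acts with intent to die. The programme may also have reached the reference population, since the article says it is being rolled out nationally. All of this is fair. It makes the direction of the net bias unknown, which is a further reason not to read a difference as an age effect.

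A reader might go further and infer that the preliminary excess is purely definitional, because 0.124/0.178 = 0.70 and a 70% readmitted share would reproduce it. The documents do not support that: the share is not given, and 13 events in 73 patients are compatible with 12.4%.

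**Conclusion.** The concern holds for the comparison and for the conclusion drawn from it. The endpoints differ, the benchmark is not shown to be adult, and the whole cohort is in a programme said to reduce re-attempts. A difference from 12.4%, in either direction, therefore cannot answer whether young first-attempters are at higher risk than adults. The Trial Status wording already goes beyond what the comparison can support.

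The size is not known. With no other bias and readmitted shares of 90% to 70%, the endpoint difference alone would move the expected figure to between 13.8% and 17.7%. The chance of declaring it high would rise from 2.2% to between 8% and 56%. These figures depend on an assumed share, a test the article does not name, and no offset from the programme, so they should not be quoted as the plan's error rate.

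Two stronger readings should be resisted. One is that the primary result is uninterpretable. It is not, because the descriptive incidence is unaffected. The other is that the bias must run upward. Readmitted re-attempts are a subset of all re-attempts only if both sources define an attempt alike, which the article does not say, and other influences may act the opposite way.

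**What to change.** - Keep the 3-month incidence of all re-attempts, with its 95% CI, as the primary result, and do not test it against 12.4%.
- Use the information on received care already gathered at follow-up to code whether each re-attempt led to hospital readmission. Compare only that proportion with 12.4%.
- Limit the youth-versus-adult conclusion, including the Trial Status sentence, unless an adult figure on the same definition is available. Whether the cited French source provides one cannot be checked from this document.
- Name the endpoint difference and the contact programme as limitations. The second still applies to the readmission-only comparison.

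The costs are a narrower claim, one coded field and revised analysis wording. Recruitment began in May 2018, so some coding will be retrospective. The article describes consulting the physician or records only when the earlier contacts fail, so for patients reached by phone the coding depends on how fully received care was recorded. Recruitment and patient care do not change.
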